### Intervention Description

#### Intervention Group

Meetings with parents in the intervention middle school will be scheduled at the beginning of school year to inform parents about HPV vaccination and explain this study to them. Consent forms will be collected during these meetings. If assemblies are forbidden by the government because of COVID-19, information meetings for parents will be cancelled. Instead, 6 interventions will be planned.

##### August-September: Program Information Sent Home to Parents via Students

Written information adapted to student age about HPV vaccination, and documents outlining objectives, interventions, constraints, foreseeable risks and expected benefits of the research, and the rights of the participants in this research context will be sent with children to give to their parents. Consent form to participate to the study to be signed by both parents or holders of parental authority and a sociodemographical questionnaire with questions about HPV knowledge will also be included.

##### October-November: Contact With Parents and Return of Information to School

Investigation team will call each authority holder individually by telephone to inform them about HPV vaccination, the study, its objective, nature of the constraints, and foreseeable risks and expected benefits of the research. The team will also remind them of the rights of participants in research and will check the eligibility criteria. Finally, when possible, the team will collect their oral consent. Parents will be asked to place the documents (consent form and sociodemographic questionnaire) in an envelope and seal it before returning it to the main teacher for reasons of data confidentiality. Documents will then be collected by the investigation team.

##### November-December: Data Collection and Student Information Sessions About Sexual Health and Vaccination

Children in the selected classes will be asked to bring in their health record on a specific date, along with the above mentioned documents, for those who forgot to return the envelope to the main teacher previously. On that day, an investigator will collect data necessary for the study in the health records (especially vaccination data) for children for whom consent form was signed by the parents. During this time, an information session about sexually transmitted diseases and vaccination will be given in class, lasting approximately 1 hour and adapted to the level of understanding (according to grade and age), in partnership with teachers. Health records will be immediately returned to the students.

##### November-December: General Practitioner Information Dissemination

A total of 88 general practitioners working in a radius of 5 km around Paul Hermann Middle School will be sent an information leaflet about HPV vaccination and cervical cancer prevention, including the latest literature review, and information about this study. If meetings are forbidden, general practitioners will be invited to a video conference call, “Around HPV,” at the beginning of school year.

##### December, February, and May (3 Campaigns): HPV Vaccination in the Health Bus

Free HPV vaccination will be offered in a health bus for girls and boys. The bus will be parked in the playground, inside the school grounds, allowing students to go there during breaks, lunchtime, or after school. Vaccination periods will be predefined, so that the recommended HPV vaccination schedules can be followed.

Vaccinations will be performed by the medical staff of the University Hospital of Reunion Island (a junior doctor under the supervision of a senior doctor) after informed consent to vaccination signed by either parents or holders of parental authority, who are invited to come along into the bus with their child.

Vaccination will be performed with nonavalent HPV vaccine. The proposed schedule is the one recommended by the marketing authorization: children aged 9 to 14 years (girl or boy): 2-dose schedule (intramuscular), with the second dose to be administered between 5 and 13 months after the first dose; children aged 15 years and older (girl or boy): 3-dose schedule (intramuscular), with the second dose to be administered at least 1 month after the first and the third at least 3 months after the second, with all 3 doses to be administered within 1 year. The vaccine label data will be documented in the health record.

Before vaccination, absence of contraindications will be checked. In case of high fever or acute illness, the vaccination will be postponed and offered at a later date. Vaccinated persons will be monitored for at least 15 minutes after vaccination in the presence of medical staff because of adverse effects that may occur in the direct aftermath of the injection (rare anaphylactic reactions, syncope (fainting) sometimes associated with falls) or psychogenic reaction to needle injection (neurological signs such as transient blurred vision, paresthesias, and tonic-clonic movements of the limbs during the recovery phase). During campaigns in February and May, the first dose of vaccination can be offered, although children will be asked to return to their general practitioner for subsequent doses.

The health bus system will be implemented as part of this study. Two students will be able to be vaccinated at a time. A child will never be left alone with an adult inside the bus; there will always be a minimum of 2 adults present. Students can take advantage of this special time on the bus to receive personalized information on sexuality and obtain free condoms.

##### June: Data Collection in Randomly Selected Classes

At the end of school year (June), an investigator will collect data from health records at a specific time during class. In particular, the researcher will look for the presence of de novo HPV vaccination performed by general practitioners outside of the health bus. Signed consent of parents or holders of parental authority will be collected before any intervention in the study (ie, before data collection and before school vaccination is carried out).

Vaccination data, even if not collected at the time of the intervention, can be collected either during the vaccination campaigns, or during the intervention at the end of school year, especially for children whose parents have agreed to participate but not to be vaccinated in the health bus. Indeed, since vaccination dates appear in the health record, it will be possible afterward to know whether pupils were vaccinated before the interventions under study in order to have the vaccination rate at the very beginning of the study.

##### July-September: Evaluation of Satisfaction and Barriers to Vaccination

Research staff will meet with students, parents, members of school staff, and general practitioners who volunteered, and semidirected interviews will be conducted to understand their satisfaction about the study and determine barriers to vaccination.

#### Control Group

In the control middle school, the study will take place at the end of school year (May-June) in 2 stages.

##### Parent Information About the Study

We will organize parent meetings to inform them of the study. If no parental meeting is possible due to the COVID-19 pandemic, parents of children in selected classes will be sent an envelope containing written information about HPV vaccination and information about the study, the sociodemographical questionnaire, and the objection form to participate to the study (data collection of health record). Thus, if the form is returned to a teacher, the investigation team will not be able to access the child’s health record. On the other hand, if no form is returned, it will be considered that parents do not object to data collection.

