### Eligibility Criteria

Inclusion criteria are as follows: enrolled in one of the classes randomly selected in the 2 middle schools designated, affiliated with or benefiting from a social security system, who will agree to participate in the study and whose parents or holders of parental authority will sign a free, informed, and written consent. Exclusion criteria (intervention group only) are as follows: hypersensitivity to the active substances or to one of the excipients of the vaccine (Gardasil 9), a permanent contraindication to vaccination, pregnant or breastfeeding (based on self-reporting), already initiated HPV vaccination (complete or incomplete schedule), or eligible to participate for collection of data but not for vaccination in the health bus; students with an incomplete vaccination schedule will be referred to their general practitioner to complete the missing doses. Vaccinations will be performed by a junior doctor under the supervision of a senior doctor.

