##### Data Collection and Student Information About Sexual Health and Vaccination

Children in the selected classes will be asked to bring in their health record on a specific date, along with the completed sociodemographic questionnaire and signed informed consent for data collection from parents. On that day, an investigator will collect data necessary for the study (especially vaccination data) in the health records for children for whom no objection form was returned. During this time, an information session about sexually transmitted diseases and vaccination will be given in class, lasting approximately 1 hour and adapted to the level of understanding (according to grade and age), in partnership with teachers. Health records will be immediately returned to the students concerned.

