The analysis of barriers to vaccination will describe the causes of nonvaccination reported for students who did not initiate the vaccination schedule. Analyses will be performed for girls and boys separately. We will also compare sociodemographic data, medical history, and health care utilization data between students who initiated HPV vaccination at the end of the school year and those who did not in the intervention group. Bivariate comparisons of percentages will be performed by the chi-square test or Fisher exact test depending on validity conditions. For continuous variables, comparisons will be made using the Student *t* test or the Mann-Whitney *U* test, depending on the conditions of validity. A multivariate analysis by logistic regression will be carried out in order to take into account confounding phenomena: the variable to be explained will be the fact of having initiated vaccination at the end of the school year, and the explanatory variables entered in the model will be the variables for which the significance threshold in bivariate analysis will be ≤.20.

To be determined in the intervention group: among students who initiated HPV vaccination at the end of school year, the proportion of students who used the health bus to initiate this vaccination. Among students who completed the full vaccination schedule at the end of school year, we will determine the proportion who completed all injections on the health bus.

In the intervention group, the proportion of students who used the health bus for sexual health information will be evaluated. In the intervention group, positive and negative points reported by students, their parents, and school staff about this program will be described. Proportion of students up to date for each type of vaccine (according to current vaccination calendar) at the end of school year, in the entire study population as well as in each of the 2 groups (intervention and control), and comparison of these proportions between the 2 groups by the chi-square test or Fisher exact test will be determined, according to validity conditions.

Analyses comparing control group to intervention group will all be performed on an intention-to-treat basis. All hypotheses will be tested with bilateral tests and *α*=.05 and confidence interval calculated at 95%. Analyses will be performed using SAS (version 9.4, SAS Institute Inc) software.

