The data recorded during this research are subject to computerized processing at the University Hospital of Reunion Island, responsible for data processing in compliance with the law no. 78-17 of January 6, 1978, relating to data processing, files, and freedoms modified by the law 2004-801 of August 6, 2004 and modified by the law no. 2018-493 of June 20, 2018. This research falls within the framework of the reference methodology (RM-001) in application of the provisions of Article 54 paragraph 5 of the amended Act of January 6, 1978, relating to information, files, and freedoms. This change was approved by decision of January 5, 2006, updated on July 21, 2016. The University Hospital of Reunion Island, responsible for data processing, has signed a commitment to comply with this reference methodology. The research sponsor undertakes to carry out the research in compliance with the General Data Protection Regulation of April 27, 2016, implemented on May 25, 2018. This research is registered in the ANSM European Union Drug Regulating Authorities Clinical Trials Database [73-2020] and at ClinicalTrials.gov [NCT04459221]. Authors obtained consent to participate in the study from participants and their parents (or holders of parental authority). Written, informed consent to participate was obtained from all participants.

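### Entry to the data appears to be by signed parental consent in the intervention school and by non-objection in the control school, and the document contradicts itself on the control rule, so the intention-to-treat comparison may lack a common denominator

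*Protocol article*

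**What the plan says.** **Intervention school.** The November-December data-collection section says that an investigator reads health records "for children for whom consent form was signed by the parents". The June data-collection section repeats the rule: "Signed consent of parents or holders of parental authority will be collected before any intervention in the study", and it counts data collection among those interventions. Consent is sought after written HPV information and an individual telephone call, in a program that offers free vaccination.

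**Control school.** Where no parent meeting is possible, Parent Information About the Study provides an objection form, and "if no form is returned, it will be considered that parents do not object to data collection". The next control-school section, on data collection, applies non-objection without the COVID-19 condition: data are collected "in the health records for children for whom no objection form was returned".

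**Text that conflicts with this.**
- That same control-school section asks children to bring their record "along with the completed sociodemographic questionnaire and signed informed consent for data collection from parents".
- Eligibility Criteria, for both schools, admits children "whose parents or holders of parental authority will sign a free, informed, and written consent".
- Data Collection and Management places data collection after signature by parents and students.
- Ethical Considerations states: "Written, informed consent to participate was obtained from all participants".

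**Analysis.** Under Statistical Methods: "Analyses comparing control group to intervention group will all be performed on an intention-to-treat basis". The primary outcome is compared by a chi-square or Fisher test, with no adjustment. Strengths and Limitations admits that exclusion criteria differ between arms, but does not mention the different consent routes.

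**The concern.** If both entry rules operated as written, a girl whose parents stay silent leaves the intervention denominator, while her counterpart in the control school stays in, provided that she brings her record. Signing a form about an HPV vaccination study is plausibly related to willingness to vaccinate. Completion could then look higher among intervention girls even if the program did nothing. The intention-to-treat label does not cure this, because the selection happens before anyone enters the dataset.

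The contradiction also matters in itself: a reader cannot tell from the document which control girls form the denominator of the primary outcome. The sample size section assumes the same 15% of nonanalyzable data in both groups, which is hard to square with two different entry rules.

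**Working it through.** **1. The plan's own figure.** Inputs from Sample Size: 6% against 20%, two-sided alpha 0.05, power 0.80. With the unpooled normal formula, n = (1.960 + 0.842)² × (0.06×0.94 + 0.20×0.80) / 0.14² = 86.7, so 87 girls per group. Then 87/0.85 = 102.4, so 103. Both stated figures reproduce. The arithmetic is sound, but it allows for no selection by consent.

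**2. Apparent coverage under selection alone.** Assumptions:
- no program effect, with 6% of all girls fully vaccinated in both schools;
- in the intervention school, the parents of every vaccinated girl sign (the extreme case);
- control girls are read by non-objection, and their record return is unrelated to vaccination;
- the consent share c is not in the document, so a range is shown.

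Apparent intervention coverage = 6%/c.

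**3. False rejection.** Intervention girls: 245/2, about 122, times c. Control girls: 259/2 × 0.85, about 110. Rejection probabilities are exact binomial sums, for the uncorrected chi-square test throughout and for a version that switches to Fisher's test when an expected count is below 5.

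| Consent c | Intervention girls | Apparent coverage vs 6% | Chi-square | Chi-square or Fisher |
|---|---|---|---|---|
| 100% | 122 | 6.0% | 5% | 5% |
| 85% | 104 | 7.1% | 6% | 6% |
| 60% | 73 | 10% | 16% | 15% |
| 50% | 61 | 12% | 31% | 26% |
| 40% | 49 | 15% | 47% | 43% |

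If the intervention arm also loses 15% of records, as the control arm does here, the chi-square-or-Fisher figures at 60%, 50% and 40% consent become 15%, 23% and 37%.

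**4. A milder assumption.** Let the parents of vaccinated girls be r times as likely to sign as the others. Apparent coverage = 0.06r/(0.06r + 0.94). For r = 2 this is 0.12/1.06 = 11.3%. With 61 intervention girls, chi-square rejects in 27% of trials.

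**5. Why girls without data must be treated alike.** Suppose that consent is 50% and unrelated to vaccination, and that the program does nothing. Scoring non-consenting intervention girls as not completed, while giving control girls without a record the observed control rate, yields 0.5 × 6% = 3% against 6%. With 122 and 130 girls, chi-square rejects in about 20% of trials, nearly all against the program. Scoring missing girls as not completed in both schools removes that asymmetry of method. It does not remove bias from unequal missingness: with data on 50% and 85% of girls, the rates are 3% and 0.85 × 6% = 5.1%, and chi-square rejects in about 12% of trials. Bounds in both arms are therefore needed too.

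**The case against.** Several stronger readings are tempting, and the document does not support them.

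- **That consenting families are compared with nearly everyone.** The objection form is tied to the case where meetings are impossible, and other sections claim written consent from all. A control girl must also bring her health record on a set date, which may itself favour health-engaged families. What stands is that the control data-collection section states non-objection without that condition, and Strengths and Limitations reports that meetings of more than 6 people were prohibited, so the contingency was live.
- **That refusing the vaccine means leaving the denominator.** Vaccination has its own consent, and the June section provides for children whose parents joined the study but declined the bus. This weakens the link between signing and vaccinating but does not break it.
- **That the bias must favour the program.** Vaccination already initiated is listed among the intervention-only exclusions, in wording that leaves unclear whether those girls' data still count. If they are removed from the analysis, early-vaccinated girls leave one arm only, and the bias could reverse.
- **That selection and effect are indistinguishable.** Vaccination dates show who was vaccinated beforehand, and the use of the health bus will be reported. These separate the two in part; doses given by general practitioners after the start remain ambiguous.
- **That consent was low.** The 29% to 42.9% cited under Sample Size is participation in a catch-up vaccination program, not consent to record reading. The expected parental veto carries no figure.

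**Conclusion.** The concern holds in a limited form. The document gives two entry rules for the two schools and contradicts itself on which one applied in the control school. The comparison labelled intention-to-treat may therefore not rest on a common denominator. Selection towards the program is plausible, but neither its size nor its net direction can be settled from the text.

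The false-rejection figures of roughly 15-16%, 26-31% and 43-47% at 60%, 50% and 40% consent are an upper-bound illustration. They rest on consent from the parents of every vaccinated girl and on assumed consent rates. At 85% consent the effect almost vanishes (about 6%). They show that the primary result could be materially distorted if consent was low, not that it was.

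**What to change.** 1. Reconcile Eligibility Criteria, the two control-school sections, Data Collection and Management, and Ethical Considerations, and state which entry rule applied in the control school.
2. Define the analysis set in both schools as all girls on the class lists of the 24 drawn classes. For girls without consent, only counts by class and sex are needed.
3. Report consent, objection and record-return rates by school.
4. Handle girls without data identically in both schools: for example, count all as not completed, with best- and worst-case bounds in both arms.
5. Show the comparison of girls with readable records alongside, and do not call it intention-to-treat.

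The article says that analyses are still ongoing, so the change is mainly wording and class-list counts. The downsides are a diluted effect estimate, wide bounds if consent was low, and residual bias if the share of girls without data differs between schools.

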##### Data Collection and Student Information About Sexual Health and Vaccination

Children in the selected classes will be asked to bring in their health record on a specific date, along with the completed sociodemographic questionnaire and signed informed consent for data collection from parents. On that day, an investigator will collect data necessary for the study (especially vaccination data) in the health records for children for whom no objection form was returned. During this time, an information session about sexually transmitted diseases and vaccination will be given in class, lasting approximately 1 hour and adapted to the level of understanding (according to grade and age), in partnership with teachers. Health records will be immediately returned to the students concerned.

### Participant Timeline

Participant timeline is displayed in Figure 1. In case assemblies are forbidden due to COVID-19 pandemic, parental meetings will be cancelled and an alternative participant timeline is displayed in Figure 2.

**Figure 1 figure1:**
[figure not shown]
Initial participant timeline. HPV: human papillomavirus.

**Figure 2 figure2:**
[figure not shown]
Participant timeline in the context of COVID-19, with meeting restrictions. HPV: human papillomavirus.

### Data Collection and Management

Data will be collected in a paper observation book after consent is signed by parents or holders of parental authority and by students. Data will be collected in the form of self-questionnaires (parents and children). Data concerning vaccination status at inclusion and at the end of the study were checked in the health record by the investigation team.

Data will be collected in paper format and will be entered into an electronic case report form (Ennov Clinical) by a clinical study technician. Data will be saved daily. A data validation plan, defined jointly by the principal investigator and the Methodology and Data Management Center (from the University Hospital of Reunion Island), will be developed and the controls to be performed will be described in detail for each variable. Once data entry is completed, the data will be checked for consistency. Inconsistencies will be reported in the CS Test module of Ennov Clinical. The data freeze/unfreeze process will be performed according to the procedure set up in the Methodology and Data Management Center.

